# Efficacy and safety of an improved Xiao-Xu-Ming-Tang traditional Chinese medicine hot compress for preventing catheter-related bladder discomfort: a multicenter, randomized, double-blind, controlled trial

**DOI:** 10.3389/fmed.2026.1799106

**Published:** 2026-04-22

**Keywords:** catheter-related bladder discomfort, hot compress, improved Xiao-Xu-Ming-Tang, protocol, randomized controlled trial

## Abstract

**Objectives:**

Catheter-related bladder discomfort (CRBD) occurs in 47–95% of patients recovering from general anesthesia, causing discomfort and increasing the risk of postoperative delirium. Xiao-Xu-Ming-Tang is a traditional Chinese medicine (TCM) concoction that has *demonstrated efficacy* in relieving urinary symptoms. Thus, we propose the use of this improved traditional Chinese medicine concoction in the form of a hot compress as an inexpensive, effective, and simple intervention for preventing postoperative CRBD.

**Methods:**

This was a multicenter, randomized, double-blind, controlled study. Ninety patients who underwent transurethral ureteral laser lithotripsy at three centers were included. Patients were randomly divided into two groups: the Chinese medicine (CM) group and the control group (salt packet (SP) group), at a ratio of 1:1. In the CM group, a hot compress (40–45 °C) of improved Xiao-Xu-Ming-Tang mixed with salt was placed above the pubic symphysis immediately after intubation. In the control group, one-tenth of the improved Xiao-Xu-Ming-Tang and salt mixture was used.

**Results:**

The *primary endpoint* is the incidence of moderate or severe CRBD at 30 min after surgery. The secondary endpoints are the incidence of moderate-to-severe CRBD, the Numerical Rating Scale (NRS) Pain score, the incidence of skin discomfort above the pubic symphysis, and the vital signs (the blood pressure, heart rate, and oxygen saturation), and patient satisfaction after surgery.

**Discussion:**

The aim of this trial was to evaluate the effect and safety of a hot compress of an improved Xiao-Xu-Ming-Tang powder and salt mixture for moderate and severe CRBD. These findings may provide a basis for the prevention of CRBD in clinical practice.

**Clinical trial registration:**

http://itmctr.ccebtcm.org.cn/, Identifier: ITMCTR2025000321.

## Introduction

1

Similar to overactive bladder, catheter-related bladder discomfort (CRBD) is mainly characterized by a frequent and urgent need to urinate as well as a burning sensation in the suprapubic region in patients recovering from anesthesia who have an indwelling catheter (1). CRBD may cause anxiety and pain, increase the need for anesthetics, and increase the incidence of postoperative complications (2). CRBD is not only a risk factor for postoperative agitation but also induces postoperative delirium in severe cases (3). Postoperative CRBD is a well-known side effect of indwelling catheter placement that occurs in 47%–95% of inpatients. Preventing or reducing the severity of CRBD is helpful for improving patients’ quality of recovery and reducing the incidence of postoperative agitation (4).

However, CRBD is difficult to prevent and treat. The main methods for preventing and treating CRBD include local anesthesia, psychological intervention and drug intervention. Currently, several methods have been proven to be effective for preventing CRBD, such as nerve block, transcutaneous electrical nerve stimulation, lidocaine, intravesical bupivacaine, magnesium sulfate, and nefopam (5–10). Because these methods are primarily implemented intraoperatively, the cost of the procedure increases. Thus, considering the substantial number of patients with indwelling catheters after surgery under general anesthesia, a cost-effective, feasible and effective strategy for preventing postoperative CRBD is needed. Traditional Chinese medicine (TCM) hot compresses have been used for more than 2,000 years. They can dilate local capillaries, improve blood circulation, reduce inflammation and swelling, dispel cold and dampness, alleviate pain and eliminate fatigue. TCM hot compresses offer a technically simple and cost-effective alternative (11, 12). TCM hot compresses can relieve pain and discomfort caused by muscle spasms as well as relieve breast tenderness and pain, post-stroke shoulder-hand syndrome and postpartum urinary retention (12–14). The improved Xiao-Xu-Ming-Tang powder is mixed with coarse sea salt (40–45 °C hot compress) to increase the skin permeability of the active components—the mild heat can dilate the suprapubic capillaries and open the skin stratum corneum pores, and the active compounds (volatile oils, alkaloids) of the medicinal materials are small molecular weight substances that can quickly penetrate the skin, enter the local subcutaneous tissue and bladder meridian, and exert anti-spasm and pain-relieving effects without systemic absorption (no systemic side effects) (15). [name], a renowned TCM expert in Shanghai, and his research team confirmed that Xiao-Xu-Ming-Tang can significantly alleviate catheter-induced bladder discomfort and irritation, as well as pain associated with urinary calculi (16). Based on clinical practice, our hospital’s TCM department optimized the original Xiao-Xu-Ming-Tang formula to form the improved version, which consists of *Notopterygii Rhizoma et Radix* (Qianghuo), *Chuanxiong Rhizoma* (Chuanxiong), *Scutellariae Radix* (Huangqin), *Ephedrae Herba* (Mahuang), *Aucklandiae Radix* (Muxiang), *Aconiti Radix Praeparata* (Zhi Fuzi), *Stephaniae Tetrandrae Radix* (Fangji), *Saposhnikoviae Radix* (Fangfeng), *Amomi Fructus* (Yangchun Sha), and *Paeoniae Radix Alba* (Sheng Baishao). The active components of these herbs have clear pharmacological effects on CRBD: *Notopterygii Rhizoma et Radix* contains volatile oils (e.g., ligustilide) and sesquiterpenoids that dilate local blood vessels and promote transdermal absorption, with its volatile components regulating the bladder meridian and relieving smooth muscle spasm; *Chuanxiong Rhizoma*, *Scutellariae Radix*, and *Ephedrae Herba* contain ephedrine (alkaloid) and volatile oils that inhibit M-cholinergic receptors of bladder smooth muscle and reduce involuntary contractions—the core pathological mechanism of CRBD—and their alkaloid components have good transdermal permeability, exerting local effects through the suprapubic skin; *Aucklandiae Radix* contains volatile oils (e.g., costunolide) for regulating qi and relieving spasm, with volatile components quickly penetrating the skin to act on local bladder meridians; *Amomi Fructus* contains volatile oils that soothe the bladder and relieve micturition urgency, with active components having high transdermal bioavailability on the lower abdominal skin. Most of these medicinal materials have a strong aromatic odor and good transdermal absorption properties; ground into powder and applied externally, they can regulate Zang-Fu organs and meridians to achieve the balance of yin and yang, which has been verified by relevant studies (17). CRBD falls under the categories of stranguria with urgency and abdominal pain in TCM, with its core pathogenesis being qi stagnation and meridian obstruction. Surgical trauma and catheter stimulation give rise to qi stagnation in the bladder meridian, which further induces bladder smooth muscle spasm. The modified Xiao-Xu-Ming-Tang is formulated based on the TCM therapeutic principles of regulating qi, unblocking meridians, and relieving spasm. The selected medicinal herbs target the bladder meridian in the lower abdomen, which accords with the standard TCM clinical practice of syndrome differentiation and treatment.

Our modification is dual-oriented: to adapt the formula for transdermal hot compress application and to achieve targeted relief of CRBD symptoms. (1) Component optimization: Based on the original prescription, Yangchun Sha and sheng Baishao were added to strengthen the actions of regulating qi, relieving spasm, and unblocking the bladder meridian, thereby exerting a targeted effect on CRBD caused by bladder smooth muscle spasm. Meanwhile, the dosages of Máhuáng and Fángjí were adjusted to reduce excessive pungency and ensure transdermal safety. (2) Formulation transformation: The original water decoction was converted into a powder mixture with coarse sea salt. The powder form increases the specific surface area of the medicinal materials, facilitating transdermal absorption. Coarse sea salt acts as a heat storage medium to maintain a stable temperature (40–45 °C) for hot compression, which is the key modification for adapting the prescription to transdermal hot compress application. (3) Efficacy re-orientation: The modified prescription abandons the systemic regulatory effect of oral administration and instead emphasizes local meridian regulation and transdermal delivery over the suprapubic region. It aims to directly alleviate bladder discomfort via the skin and meridians, which better matches the clinical demand for perioperative local intervention in CRBD.

Therefore, we hypothesized that improved traditional Chinese medicine hot compresses could reduce the incidence of moderate-to-severe CRBD in patients, providing a new method for preventing CRBD.

## Methods and analysis

2

### Study design

2.1

This is a multicenter, randomized, parallel group controlled study. The study period is November 2024–November 2025. A 24-h observation period will be included in the study (pictured). Patients who provide written informed consent will be tentatively enrolled and screened for eligibility during the observation period. In the experimental group, a hot compress (40–45 °C) of a Xiao-Xu-Ming-Tang and salt mixture will be placed above the pubic symphysis immediately after intubation. In the control group, a hot compress (40–45 °C) of one-tenth of an improved Xiao-Xu-Ming-Tang (This dose was confirmed to be non-therapeutic for CRBD based on our pre-experimental data and clinical dosage principles, cannot produce a significant effect on relieving bladder discomfort) and sea salt mixture will be placed above the pubic symphysis. During the observation period, the severity of CRBD will be graded using a scoring system developed and used by Agarwal et al. (18). The severity of CRBD will be divided into 4 grades: grade 1, the patient reports no symptoms of urinary tract or bladder discomfort; grade 2, the patient reports mild urinary tract or bladder discomfort only after prompting; grade 3, the patient reports moderate urinary tract or bladder discomfort without prompting but does not exhibit any behavior alluding to the discomfort; and grade 4, the patient reports severe urinary tract or bladder discomfort. The behaviors alluding to discomfort included flailing limbs, a strong vocal response, and attempts to remove the catheter.

*Experimental group (Composition of the TCM formulation)*: 9 g Qianghuo, 9 g Chuanxiong, 9 g Huangqin, 6 g Mahuang, 9 g Muxiang, 9 g Prepared *Aconitum Carmichaelii* Radix, 6 g Fangji, 9 g Fangfeng, 6 g Yangchun Sha, 9 g Sheng Baishao (full dose of improved Xiao-Xu-Ming-Tang) are ground into powder, mixed thoroughly with 100 g coarse sea salt, packed into a breathable cloth bag, heated to 40–45 °C, and applied as a hot compress above the pubic symphysis immediately after intubation until 60 min after surgery.

*Control group*: one-tenth of the full dose of improved Xiao-Xu-Ming-Tang powder (the proportion of each medicinal material is consistent with the experimental group), mixed thoroughly with 100 g coarse sea salt, packed into a breathable cloth bag, heated to 40–45 °C, and applied as a hot compress above the pubic symphysis immediately after intubation until 60 min after surgery.

*Supplemented the quality control details of the herbal powder*: A strict quality control system is implemented for the herbal powder:

*Preparation process quality control*: The grinding, mixing, and packaging processes are carried out in a GMP-compliant TCM preparation room; each batch of powder is sampled for active component content detection, and unqualified batches are discarded.

*Storage and transportation quality control*: The powder is stored in a sealed, dry, and cool environment (25 °C, relative humidity <60%); the hot compress bags are transported to each research center in a sealed carton, and the batch number and production date are marked to ensure traceability.

The study will be conducted in three general hospitals in China: Shanghai General Hospital, Shanghai Fourth People’s Hospital, and the First Affiliated Hospital of Xiamen University. The main research center is Shanghai General Hospital, and the principal investigator is [name]. All evaluators will receive online centralized training and complete the assessment at each research center after passing the assessment.

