### Randomization and masking

2.4

An envelope lottery will be used to randomize patients into groups, and because the study will be conducted across 3 centers, stratified randomization is required, with 30 patients included from each center, 15 of whom will be assigned to the experimental group and the remaining 15 will be included in the control group. The study will be conducted in double-blinded manner, and patients were only informed that they were enrolled in a clinical trial for the prevention of postoperative CRBD and were assigned to a study group with a unique study number, and the specific grouping (experimental/control) and the differences in the composition of the hot compress bags (full dose/one-tenth dose of medicinal powder) were not disclosed to the patients at any stage before, during, or after the surgery. The hot compress will be placed over the patient’s pubic symphysis immediately after intubation under general anesthesia and removed 60 min after surgery by a site nurse who will not be involved in follow-up visits. Patients, anesthesiologists, surgeons, note-takers, data registrars and analysts will be unaware of the group assignments. The TCM package will be distributed to each center by the Department of TCM of Shanghai Fourth People’s Hospital. Both groups will emit the smell of TCM, which are indistinguishable by odor alone. Group assignments will be maintained by the personnel at the main site who are not involved in the study but rather responsible for the study group numbers and hot compresses. Only when the patient has a serious adverse reaction that is suspected to be related to the intervention itself will he or she be responsible for the emergency unblinding of the patient to ensure timely treatment of the condition.

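### The two compress bags differ by about 73 g of fill (181 g against 108 g), with no filler stated and only smell matched, so blinding by weight, bulk and look is not secured

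*Protocol article*

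**What the plan says.** Section 2.1 lists the ten herbs of the experimental bag by weight: "9 g Qianghuo, 9 g Chuanxiong, 9 g Huangqin, 6 g Mahuang, 9 g Muxiang", then "9 g Prepared *Aconitum Carmichaelii* Radix", then "6 g Fangji, 9 g Fangfeng, 6 g Yangchun Sha, 9 g Sheng Baishao". The control bag receives "one-tenth of the full dose of improved Xiao-Xu-Ming-Tang powder", with the herbs in the same proportions. In both arms the powder is "mixed thoroughly with 100 g coarse sea salt, packed into a breathable cloth bag, heated to 40–45 °C". No other ingredient is named for either bag. In both arms the bag is "applied as a hot compress above the pubic symphysis immediately after intubation until 60 min after surgery".

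On masking, Section 2.4 says: "Both groups will emit the smell of TCM, which are indistinguishable by odor alone". Section 2.6 likewise gives smell as the property on which the groups cannot be told apart. Weight, bulk, feel and appearance are not mentioned. Section 2.4 also states: "Patients, anesthesiologists, surgeons, note-takers, data registrars and analysts will be unaware of the group assignments". Under Section 2.8.3 a dedicated follow-up researcher scores pain and sedation, and the discomfort grades are recorded at the same times. Neither that researcher nor the recovery-room staff appear by title among the blinded roles.

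The primary outcome (Section 2.2.1) is moderate or severe bladder discomfort 30 min after surgery. The Discussion acknowledges that this outcome is subjective.

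**The concern.** The trial is presented as double-blind in its title, Section 2.4 and its Conclusion. The control bag loses nine-tenths of the powder and gains nothing in its place, so the two bags cannot weigh the same or be filled to the same extent. Matching the smell does not conceal that.

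The timing matters. The bag is still on the patient at the 30 min assessment, so anyone grading discomfort then may see it. Each centre is to treat 15 patients per arm, so recovery staff and the assessor will meet both kinds of bag many times and could learn to tell them apart.

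The outcome is open to influence. In the Section 2.1 scale, the step from grade 2 to grade 3, which is the step that defines an event, turns on whether the patient volunteers the complaint or reports it only when asked. An assessor who suspects the arm could shift that boundary without intending to. A difference between arms could then appear without any herb effect.

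**Working it through.** **The plan's own figure.** The article states no bag weight. Its only computed figure is the sample size in Section 2.6: 70% against 35%, two-sided α = 0.05, power 90%, ratio 1:1.

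- Pooled-variance formula, mean proportion 0.525: n = [1.960·√(2·0.525·0.475) + 1.282·√(0.70·0.30 + 0.35·0.65)]² / 0.35² = 40.7, so 41 per arm. The plan states 42.
- Loss of 5%: 42 / 0.95 = 44.2, so 45 per arm, as stated.

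The sample size reproduces to within one patient per arm, and the present point does not affect it.

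**Fill mass (inputs from Section 2.1, excluding the cloth).**

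- Powder, full dose: 7 × 9 g + 3 × 6 g = 63 + 18 = 81 g
- Powder, control: 81 / 10 = 8.1 g

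| | Powder | Salt | Total fill | Powder share |
|---|---|---|---|---|
| Experimental | 81 g | 100 g | 181 g | 81/181 = 45% |
| Control | 8.1 g | 100 g | 108.1 g | 8.1/108.1 = 7% |

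- Difference: 181 − 108.1 = 72.9 g
- Ratio: 181 / 108.1 = 1.67
- The control fill is 72.9 / 181 = 40% lighter.

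**Bulk (assumption).** The article gives no densities. With bulk density 1.0–1.3 g/mL for salt and 0.3–0.7 g/mL for powder, fill volume is 100/ρ(salt) + powder/ρ(powder). The ratio of experimental to control runs from (100/1.0 + 81/0.7) / (100/1.0 + 8.1/0.7) = 216/112 = 1.9 to (100/1.3 + 81/0.3) / (100/1.3 + 8.1/0.3) = 347/104 = 3.3. The direction is certain; the size depends on the assumption.

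**Heat capacity (assumption).** With specific heat 0.85–0.90 J/g/K for salt and 0.8–2.0 J/g/K for powder:

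- Lowest ratio: (100·0.90 + 81·0.8) / (100·0.90 + 8.1·0.8) = 155/96 = 1.6
- Highest ratio: (100·0.85 + 81·2.0) / (100·0.85 + 8.1·2.0) = 247/101 = 2.4

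Total heat capacity is larger in the experimental bag for any positive specific heat of the powder. This says nothing yet about skin temperature.

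**Timing.** The bag comes off 60 min after surgery and the primary assessment is at 30 min after surgery, so it is in place with 30 min to run.

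**Illustration of what a reporting bias would do.** Suppose the herbs have no effect, and bias alone lowers the reported rate in the experimental arm from 70% (the plan's control rate) by 10 or 15 points. Both shifts are assumptions. With 45 per arm and the uncorrected chi-square test, rejection probability ≈ Φ[(d − 1.960·s₀)/s₁], where s₀ is the pooled and s₁ the unpooled standard error.

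- 70% vs 60%: s₀ = 0.1006, s₁ = 0.1000; Φ[(0.10 − 0.1971)/0.1000] = Φ(−0.97) ≈ 0.17
- 70% vs 55%: s₀ = 0.1021, s₁ = 0.1008; Φ[(0.15 − 0.2000)/0.1008] = Φ(−0.50) ≈ 0.31

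Exact binomial enumeration gives 17% and 31% as well, against a nominal 5%.

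**The case against.** A reader might infer from the masses that the double-blind fails outright. The article does not support that.

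- In a parallel-group trial each patient has one bag and nothing to compare it with.
- Section 2.4 says the dose difference is never disclosed to patients, so a patient who feels the bag has no reason to read its weight as an allocation.
- The bag is placed under anaesthesia, and the nurse who handles it takes no part in follow-up.
- Allocation is held by separate personnel, and patients carry study numbers.

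These safeguards stand and narrow the risk for patients. They do not cover staff who see both kinds of bag.

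A reader might also infer that a heat effect is mixed into the herb comparison. The Introduction names the salt as the heat store, and its amount is equal in both arms. Section 2.8.2 requires 40–45 °C at the contact surface, continuously monitored by probe, with no distinction by arm. A difference in delivered skin temperature is therefore not shown. Cooling or reheating could still differ, because total heat capacity does.

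On the assessor, the list in Section 2.4 includes note-takers and data registrars, which may be meant to cover the follow-up researcher. The wording leaves this unclear; it is not evidence of an unblinded assessor.

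The 17% and 31% figures assume a uniform, one-directional bias of a size the article does not support. They show what such a bias would do and do not measure this defect.

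Finally, a condensed article may leave outer covers to the full protocol. But it does state both compositions in full, and as stated they do not match.

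**Conclusion.** The point holds as a gap in the masking plan. The stated recipes give fills of 181 g and 108.1 g, 72.9 g apart (ratio 1.67). This is exact arithmetic from Section 2.1 and needs no assumption beyond the absence of an unstated filler. The article claims matching on smell only, so concealment by weight, bulk and look is not secured. The parties most exposed are recovery staff and the researcher assessing discomfort at 30 min; patients are less so.

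Actual unblinding is not demonstrated, and neither is a heat confound. The bulk ratio (1.9 to 3.3), the heat-capacity ratio (1.6 to 2.4) and the false-positive figures all rest on assumed inputs. The matter is worth correcting because the endpoint is subjective and the correction is cheap.

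**What to change.** Keep the herb content of both bags as stated. Then:

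1. Bring the control bag to the same mass and bulk with an inert, similarly coloured filler, and state this in Section 2.1.
2. Put both bags in identical opaque covers coded by study number only.
3. In Section 2.4, name the researcher assessing bladder discomfort and the recovery staff among the blinded roles, and say how weight, bulk and look are matched.
4. Add an arm-guess question for assessors and report the result. Ask patients only if the question is worded so that it does not reveal the dose difference.

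The cost is a small packing effort and one case report form item.

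The stated study period ended in November 2025, so the bags may already have been used. If they were unmatched, the trial report should give the weight difference and the assessor's blinding status, and qualify the double-blind claim accordingly.

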### Outcomes

2.2

#### Primary outcomes

2.2.1

The primary outcomes will be the incidences of moderate and severe CRBD (grades 3 and 4) at 30 min after surgery.

#### Secondary outcomes

2.2.2

The five secondary outcomes are as follows: (1) the incidence of moderate-to-severe CRBD at 1 h, 6 h, and 24 h after surgery; (2) the NRS score, which is used to evaluate postoperative pain, at 30 min, 1 h, 6 h, and 24 h after surgery, with scores ranging from 0, indicating no pain, to 10, indicating the worst pain imaginable; (3) the incidence of skin discomfort above the pubic symphysis (scald, redness, pruritus, allergy, etc.); (4) vital signs (blood pressure, heart rate, and oxygen saturation) at 10, 20, 30, 40, 50 min, 1 h, 6 h, and 24 h after surgery; and (5) patient satisfaction [24 h after surgery, patient satisfaction using a 5-point scale, with items graded 1 (“very dissatisfied”) to 5 (“very satisfied”)].

